## Reporting Procedure

### AEs and SAEs

All adverse events and serious adverse events that should be reported as defined in section 8.1.1 will be recorded in the patient's CRF.

SAEs must be reported by the investigator to the sponsor, within 24 hours after the site has gained knowledge of the SAE. Every SAE must be documented by the investigator on the SAE pages (to be found as part of the CRF). The Serious Adverse Event Report Form must be completed, signed and sent to the sponsor. The initial report shall promptly be followed by detailed, written reports if necessary. The initial and follow-up reports shall identify the trial subjects by unique code numbers assigned to the latter.

The sponsor keeps detailed records of all AEs reported by the investigators and performs an evaluation with respect to seriousness, causality and expectedness. Investigators will if necessary exclude patient from the trial.

### SUSARs

SUSARs will be reported to the Competent Authority and Ethics Committee according to national regulation. The following timelines should be followed.

The sponsor will ensure that all relevant information about suspected serious unewpeted adverse reactions that are fatal or life-threatening is recorded and reported as soon as possible to the Competent Authority and Ethics ommittee in any case no later than seven (7) days after knowledge by the sponsor of such a case, and hat relevant follow-up information is subsequently communicated within an additional eight (8) days.

All other suspected serious unexpected adverse reactions will be reported to the Comptent Authority concerned and to the Ethics Comitee concerned as soon as possible, but within a maximum of fifteen (15) days of first knowledge by the sponsor.

SUSAR will be reported using the CIOMS form from www.legemiddelverket.no.

### Annual Safety Report

Once a year throughout the clinical trial, the sponsor will provide the Competent Authority with an annual safety report. The format will comply with national requirements.

### Clinical Study Report

The adverse events and serious adverse events occurring during the study will be discussed in the safety evaluation part of the Clinical Study Report.

## Procedures in Case of Emergency

The investigator is responsible for assuring that there are procedures and expertise available to cope with emergencies during the study.

If a patient experiences a SUSAR (see above), unblinding will be perfomed immediately, and before it is reported to the Competent Authority. To avoid unblinding of other study patients, information regarding whether the patient has received oxytocin or placebo will be kept in separate sealed envelopes, one for each patient with the drug-package numberwritten on the outside. The envelopes will be kept in a locked cabinet in the treatment facility. If necessary, the nurse on duty will contact the primary investigator or his representant at Lade Behandlingssenter to get knowledge of the location of the envelopes, open the envelope with the patient’s study ID, and unblind the patient.

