## Database management

When enrolled in the project, patients will have a study form with both name/national identity code and study ID. At discharge, these forms connecting the patient’s identity to the Study ID will be kept separately, and the data with only Study ID as identifying code will be transformed to a secondary study form containing only the Study ID for further analysis. The data linking patient ID to study ID will be transferred to the Unit of Applied Clinical Research for storage in accordance with national regulations, for 15 years after the termination of the study. Randomisation code is kept with the Unit of Applied Clinical Research until code can be broken.

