### Blinding and emergency unblinding

Patient, investigator, personnel assessing outcomes and data analyst are blinded during this study. The randomization will be done electronically by the nurse on duty which will have an instruction sheet for further administration of the spray compound. The randomization prosess provides a drug package number corresponding with the Study ID-number of the patient. Neither the clinicians/staff nor the patients will know which spray bottles contain the active drug. The protocol linking the ID-numbers to the randomization will be kept at the Unit of Applied Clinical Research and will not be revealed to the researchers until a study arm is completed. In case of emergency, unblinding will be perfomed immediately and before it is reported to the Authority. To avoid unblinding of other study patients as well, information regarding whether each patient has received oxytocin or placebo will be kept in separate sealed envelopes, one for each patient. See also section 8.6.

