# Appendix D – example of labelling

|  | |
| --- | --- |
| **Oxytocin/placebo nesespray til klinisk utprøving**  **for hjemmebruk**  (Batchnr, produksjonsdato, legemiddelform, etc) | |
|  | |
| *Protokollnr:* | 140682 |
| *EudraCTno:* | 2015-004463-37 |
| *Ved spørsmål, kontakt:* | [name] |
|  | Tlf [name]  [[contact]](mailto:[contact])  [name] |
| *Åpnet dato:* | Åpent felt til å skrive i |
| *Studiespesifikk pasientkode:* | Åpent felt til å skrive i |
| For hjemmebruk: **1 spray i hvert nesebor inntil 3 ganger daglig**.  Utløpsdato:Åpent felt til å skrive i  **Anvendes senest 6 mndr etter produksjonsdato. Uåpnet pakning skal oppbevares kaldt.**  **Holdbarhet: 1 mnd etter åpning. Oppbevares i romtemperatur.** | |
| **Oppbevares utilgjengelig for barn.** | |

|  | |
| --- | --- |
| **Oxytocin/placebo nesespray til klinisk utprøving**  **ved Lade Behandlingssenter**  (Batchnr, produksjonsdato, legemiddelform, etc) | |
|  | |
| *Protokollnr:* | 140682 |
| *EudraCTno:* | 2015-004463-37 |
| *Ved spørsmål, kontakt:* | [name] |
|  | Tlf [name]  [[contact]](mailto:[contact])  [name] |
| *Åpnet dato:* | Åpent felt til å skrive i |
| *Studiespesifikk pasientkode:* | Åpent felt til å skrive i |
| For bruk i instutisjon: **3 sprayer i hvert nesebor kl 09.00 og kl 18.00**.  Utløpsdato: Åpent felt til å skrive i  **Anvendes senest 6 mndr etter produksjonsdato. Uåpnet pakning skal oppbevares kaldt.**  **Holdbarhet: 1 mnd etter åpning. Oppbevares i romtemperatur.** | |
| **Oppbevares utilgjengelig for barn.** | |

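### Section 8.6 unblinds every SUSAR through envelopes held at the site, so a code break for regulatory reporting is not kept apart from one needed for the patient's care

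*Protocol*

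**What the plan says.** Protocol section 8.6 sets the trigger: "If a patient experiences a SUSAR (see above), unblinding will be perfomed immediately, and before it is reported to the Competent Authority". It then gives the mechanism. There is one sealed envelope per patient, and "The envelopes will be kept in a locked cabinet in the treatment facility". Each envelope is marked on the outside: "one for each patient with the drug-package numberwritten on the outside". In a step that is conditional on need, "the nurse on duty will contact the primary investigator or his representant at Lade Behandlingssenter to get knowledge of the location of the envelopes", and is then to open the envelope bearing the patient's study ID.

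Section 10.2.2 states who is blind: "Patient, investigator, personnel assessing outcomes and data analyst are blinded during this study". It also provides for immediate unblinding, but the trigger there is an emergency. It too places unblinding before the report to the authority, describes the same individual envelopes, and refers to 8.6. It adds that randomization yields a drug-package number corresponding to the patient's Study ID.

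Section 8.5.1 gives the classification of events to the sponsor, who "performs an evaluation with respect to seriousness, causality and expectedness". Section 8.5.2 allows the sponsor 7 days to report a fatal or life-threatening SUSAR and 15 days for any other. On custody of the code, section 9.5 says: "Randomisation code is kept with the Unit of Applied Clinical Research until code can be broken".

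**The concern.** A code break can serve two purposes. One is clinical: the treating team needs the arm in order to manage the patient, and needs it at once, on site. The other is regulatory: the safety report needs the arm, but only the person preparing the report has to know it. Section 8.6 uses the regulatory category as the trigger and the clinical mechanism as the route. The code-holding unit is given no part in SUSAR disclosure, and nothing limits who at the site may learn the result.

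At stake is the blind for the affected patient. Oxazepam dose, a phase 1 primary endpoint, follows staff-scored CIWA-Ar (sections 6.2.1 and 7.2), and several of those items are scored by observation. The phase 2 primary endpoints, time to relapse and amount of alcohol, rest largely on the patient's notebook and Time-Line Follow-back. The intention-to-treat population keeps such a patient in the analysis.

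Separately, section 8.6 marks the envelope with one identifier and tells the nurse to look for another. That adds a look-up step at the moment when speed and certainty matter most.

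**Working it through.** **1. The texts side by side**

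| Question | Section 8.6 | Section 10.2.2 | Elsewhere |
|---|---|---|---|
| Trigger | Any SUSAR | Emergency | – |
| Must the arm be needed for care? | Not required | Not stated, though implied by the word emergency | – |
| Timing | Immediate, before the authority report | Immediate, before the authority report | 7 or 15 days to report (8.5.2) |
| Who decides that it is a SUSAR | – | – | Sponsor (8.5.1) |
| Where the arm can be found | Envelopes at the site | Code-holding unit, plus envelopes | Code-holding unit (9.5) |
| Who opens | Nurse on duty, if needed | Not stated | – |
| Envelope identifier | Drug-package number on the outside; study ID in the instruction | The two numbers correspond | – |

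The reporting chain runs from site to sponsor (within 24 hours), then to the sponsor's evaluation, then to the authority (7 or 15 days). No link in it requires anyone on the ward to know the arm.

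**2. Yardstick for size**

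This point contains no figure of the plan's own. The yardstick is the 10 mg difference in section 10.1, with SD about 10 mg. The plan's sample size reproduces by the normal approximation, taking alpha as two-sided: n = 2 × (1.960 + 0.842)² × 10² / 10² = 15.7, so 16 per group. With 40 patients allocated 1:1, each arm has about 20.

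**3. Effect of one break on oxazepam**

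The envelopes are individual, so one break exposes one patient: 1/40 = 2.5% of the trial, or 1/20 = 5% of an arm. If the break changed that patient's total by x mg, the arm mean moves by x/20. The values of x are assumptions; 60 mg is the top of the local range quoted in section 10.1.

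| x (mg) | Shift in arm mean (mg) | Share of 10 mg |
|---|---|---|
| 10 | 0.5 | 5% |
| 15 | 0.75 | 7.5% |
| 30 | 1.5 | 15% |
| 60 | 3.0 | 30% |

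This applies only if the break falls within the 3 inpatient days. If the patient were instead lost from the comparison (19 against 20), exact t-test power would go from 86.9% to 86.0%.

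**4. How often**

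The protocol gives no SUSAR rate. The chance of at least one event among 40 is 1 − (1 − p)^40. For assumed p of 0.1%, 1%, 2% and 5% per patient, it is 3.9%, 33%, 55% and 87%. Section 8.2 describes the product as well tolerated and does not count withdrawal seizures or delirium tremens as SAEs, which points to the low end.

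**The case against.** The strongest reply is that the two sections, read together, do more than 8.6 alone suggests. Most of that reply stands, and it rules out several stronger readings.

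- A reader might infer that an emergency that is not a SUSAR has no route. Section 10.2.2 provides one, with the same envelopes, and section 8.6 is itself headed as an emergency procedure. What is missing is a separation of purposes.
- A reader might infer that the nurse opens an envelope for every SUSAR and that the CIWA-Ar raters thereby lose the blind. The nurse's step is conditional, and the sentence ordering unblinding names no actor. No text makes the nurse on duty the rater; section 8.2 speaks only of trained medical staff. The investigator or representative is contacted about where the envelopes are, and is not said to learn the arm.
- A reader might infer that the envelope cannot be matched to the patient. Section 10.2.2 says the two numbers correspond, so this is a look-up and not a dead end.
- A reader might infer that the labels are defective because the field "Studiespesifikk pasientkode" is blank. Appendix D is an example, and that field is marked for writing in.

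Timing also limits the harm. The site has up to 24 hours to report, and the sponsor then classifies the event, so much of the 3-day oxazepam window may have passed. A patient with such an event may also stop treatment.

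The reply does not remove the rule itself. As written, every SUSAR is unblinded regardless of clinical need, and the only described way to do it brings the arm to the site.

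**Conclusion.** The point holds as a limited defect. Sections 8.6 and 10.2.2 merge regulatory and emergency code breaks. They allow site staff to learn the arm for a purpose that the code-holding unit could serve, and this sits badly with the blinding statement in 10.2.2. The two identifiers in 8.6 add an avoidable step.

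The size is small. It is one patient per event and, under the assumed distortions, at most 3.0 mg in an arm mean against a 10 mg target. Oxazepam is touched only if the break comes during the inpatient days. Later self-reported outcomes are touched only if the patient continues and learns the arm, and the protocol does not say whether the patient is told. The event rate and the size of any distortion are assumptions. The case for changing the text is that the exposure serves no purpose and costs little to remove; it is not that the trial's result is in danger.

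**What to change.** Amend sections 8.6 and 10.2.2 together:

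1. For SUSAR reporting, the Unit of Applied Clinical Research discloses the arm only to the sponsor's safety reporter. Ward staff, investigator, outcome assessors and analyst stay blinded.
2. Site envelopes are used only for emergency breaks in which knowledge of the arm is needed for the patient's care, whatever the event's regulatory class. Each opening is recorded.
3. The Study ID and the drug-package number both appear on the outside of every envelope.

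The cost is revised wording in two sections, re-marked envelopes, and a contact at the unit for code requests. The one real downside is that the unit must be able to answer within the 7-day and 15-day reporting limits.

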# Data management and monitoring

## Case Report Forms (CRFs)

The designated investigator or staff will enter the data required by the protocol into the Case report forms (CRF). The Principal Investigator is responsible for assuring that data entered into the CRF is complete, accurate, and that entry is performed in a timely manner. If any assessments are omitted, the reason for such omissions will be noted on the CRFs. Corrections, with the reason for the corrections will also be recorded.

After database lock, the investigator will receive paper copies of the subject data for archiving at the investigational site.

Type of CRF used: WebCRF.

## Source Data

The medical records for each patient should contain information which is important for the patient’s safety and continued care, and to fulfill the requirement that critical study data should be verifiable.

To achieve this, the medical records of each patient should clearly describe at least:

- That the patient is participating in the study, e.g. by including the enrollment number and the study code or other study identification;
- Date when Informed Consent was obtained from the patient and statement that patient received a copy of the signed and dated Informed Consent;
- Results of all assessments confirming a patient’s eligibility for the study;
- Diseases (past and current; both the disease studied and others, as relevant);
- Surgical history, as relevant;
- Treatments withdrawn/withheld due to participation in the study;
- Results of assessments performed during the study, including CIWA-scores;
- Treatments given, changes in treatments during the study and the time points for the changes;
- Number of nasal spray bottles;
- Visits to the clinic / telephone contacts during the study, including those for study purposes only;
- Non-Serious Adverse Events and Serious Adverse Events (if any) including causality assessments;
- Date of, and reason for, discontinuation from study treatment;
- Date of (and reason for) withdrawal from study;
- Date of death and cause of death, if available;
- Additional information according to local regulations and practice.

The records for each subject should contain information which is important for the subject’s safety and to fulfill the requirement that critical study data should be verifiable.

## Study Monitoring

A clinical study monitor will visit the investigator in a regular basis according to the monitor plan. A monitoring plan specific to this study is held separately to the protocol. The monitoring plan outlines the level of monitoring to be performed for the trial and how this will be carried out. The level of monitoring is based on the phase of the trial and any perceived risks. Monitoring visits will commence after the Sponsor approves the plan.

Monitor at AKF, NTNU and the study team has agreed that the study is going to be monitored according to a medium risk. This means that 20 % of all data entered in the study CRF is going to be source data verified, all patient informed consents will be controlled, All SAEs and the primary endpoint in the study will also be fully monitored.

ISF/TMF will be monitored and the monitor will confirm that the study is conducted in compliance with ICH-GCP, approved research protocol and other relevant laws and regulations. Study drug accountability will also be monitored.

## Confidentiality

The investigator shall arrange for the secure retention of the patient identification and the code list. Patient files shall be kept for the maximum period of time permitted by each hospital. The study documentation (CRFs, Site File etc) shall be retained and stored during the study and for 15 years after study closure. All information concerning the study will be stored in a safe place inaccessible to unauthorized personnel.

## Database management

When enrolled in the project, patients will have a study form with both name/national identity code and study ID. At discharge, these forms connecting the patient’s identity to the Study ID will be kept separately, and the data with only Study ID as identifying code will be transformed to a secondary study form containing only the Study ID for further analysis. The data linking patient ID to study ID will be transferred to the Unit of Applied Clinical Research for storage in accordance with national regulations, for 15 years after the termination of the study. Randomisation code is kept with the Unit of Applied Clinical Research until code can be broken.

# Statistical methods and data analysis

## Determination of Sample Size

In a previous study in patients receiving intranasal oxytocin ^17^, the mean dose lorazepam given was 3.4 mg in the oxytocin group and 16.5 mg in the control group. These doses correspond to about 60-70 mg oxazepam and about 320-340 mg oxazepam, respectively. The difference found in that study as well as the does used are, however, rather extreme, and far outside the doses used in both in Norway in general and at Lade Addiction Treatment Center. At Lade Addiction Treatment Center, the oxazepam doses generally range from 0 to 60 mg, with an estimated mean of about 20-30 mg and a SD of about 10 mg. As a difference of 10 mg in oxazepam consumption is of clinical interest to detect between groups, 16 patients in each group are required given an alpha value of 0.05 and a power of 80 %. Therefore, a total of 40 patients will be included in the study.

## Randomization

Randomization will be performed by Unit of Applied Clinical Research, NTNU.

### Allocation- procedure to randomize a patient

Preparation of active drug or placebo will produce identical nasal sprays. Who to receive the active drug will be determined by electronic randomization executed with WebCRF, provided by the Unit of Applied Clinical Research at the Norwegian University of Science and Technology (NTNU). More information on the randomization services from the Unit of Applied Clinical Research can be found at <http://www.ntnu.edu/dmf/akf/randomisering>.

### Blinding and emergency unblinding

Patient, investigator, personnel assessing outcomes and data analyst are blinded during this study. The randomization will be done electronically by the nurse on duty which will have an instruction sheet for further administration of the spray compound. The randomization prosess provides a drug package number corresponding with the Study ID-number of the patient. Neither the clinicians/staff nor the patients will know which spray bottles contain the active drug. The protocol linking the ID-numbers to the randomization will be kept at the Unit of Applied Clinical Research and will not be revealed to the researchers until a study arm is completed. In case of emergency, unblinding will be perfomed immediately and before it is reported to the Authority. To avoid unblinding of other study patients as well, information regarding whether each patient has received oxytocin or placebo will be kept in separate sealed envelopes, one for each patient. See also section 8.6.

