
## Rationale for the Study and Purpose

The study will be conducted at Lade Addiction Treatment Center, Norway. 40 consecutively admitted in-patients undergoing medical detoxification from alcohol at Lade Addiction Treatment Center will be included in the study. In 2014, 150 patients with alcohol dependency as their primary diagnosis were admitted electively to the detoxification unit. If the enrollment of the target number of inclusions exceeds 12 months, the study will seek to include patients from the Clinic of Substance Use and Addiction Medicine at St. Olav’s Hospital.

Oxytocin is neuropeptide hormone which, to our knowledge, is not associated with severe adverse effects. It is a world-wide used, approved, licensed and recommended medicine indicated for the initiation or improvement of uterine contractions in order to achieve vaginal delivery for fetal or maternal reasons. Oxytocin nasal spray is also commonly used by mothers when breastfeeding in the therapy and prophylaxis of mastitis. The potential benefits of the drug as an alternative to benzodiazepine against alcohol withdrawal symptoms, and the benefits of the study are considered greater than the health risks.

In a double blind, prospective randomized parallel group placebo-controlled trial patients will be assigned to receive either oxytocin or placebo which will be administered as a nasal spray twice daily during 3 days of inpatient detoxification, and as a self-administrated spray during a 4-week follow-up period. One arm will receive oxytocin nasal spray, the other arm placebo spray. Patients are randomized in a 1:1 ratio to oxytocin or placebo. The oxytocin will be administered as Syntocinon nasal spray. Syntocinon contains synthetic oxytocin for intranasal use containing 6.7 μg per dose. 1 IU varies between 1.7 μg and 2.2 μg. With 1 IU = 1.7 μg, 1 μg = 0,588 IU, which makes 6.7 μg = 4.34 IU, for practical use 4 IU per dose. We are planning to use 6 insufflations and in total 24 IU given twice daily. This is the same dose of oxytocin as given in a pilot study on human subjects, in which no adverse side effects were reported. The oxytocin dose used by breast-feeding mothers is 6.7 μg.

The placebo spray contains the same ingredients as Syntocinon, except oxytocin.

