# Overall STUDY Design

The study is a phase III.

Double blind, prospective randomized parallel group placebo-controlled trial.

4 weeks outpatient treatment

Day 1-3: In-patient

treatment

On admission

____________________________________________________________________________________________
Main assessments Study entry Discharge Follow-up
 D0 D2 D3 D30 + D60

Arm 2:Placebo

Arm 1: Oxytocin

| Study Period | Estimated date of first patient enrolled: 01.10.2016  Anticipated recruitment period: 12 months  Estimated date of last patient completed: 01.10.2017 |
| --- | --- |
| Treatment Duration: | 3 days in-patient treatment, followed by 4 weeks outpatient treatment and a phone interview at 8 weeks. |
| Follow-up: | Check-point at 4 weeks during 4-week outpatient treatment, phone interview at 8 weeks |

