## Number of Patients

40 patients will be included in this trial.

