### During Treatment, D1-D3

CIWA-Ar registrations are performed to monitor abstinence severity; these measturements include blood pressure and heart rate. Since CIWA-Ar is symptom driven, there are no exact times for these measurements. Nasal spray is given twice daily, at 0900h and at 1800h. The nasal spray container is weighed at the end of the inpatient period.

Day 3; at discharge: Actigraphs are handed in. Blood and urine samples are obtained. Patients are asked to fill out questionnaires at day 3, see table in section 7.3. Patients are instructed in the use of nasal spray as needed for the next 4 weeks. They will receive a notebook in which they will keep a log of use of the study drug, any intake of concomitant medication etc., and possible adverse events.

### End of Treatment and End of Study Visit, D 30

Clinical status with vital signs and laboratory tests is repeated. Patients fill out questionnaires (see table in section 7.3), and hand in nasal sprays and their notebooks. Nasal spray containers are weighed. A phone interview will be done at day 60.

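### The protocol's only code-release trigger is completion of one study arm, which contradicts its statement that all parties stay blinded during the study; the expected effect is modest

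*Protocol*

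**What the plan says.** Section 10.2.2 of the protocol opens with a general rule: "Patient, investigator, personnel assessing outcomes and data analyst are blinded during this study". Later in the same paragraph it says that the list linking ID numbers to the randomisation is held by the Unit of Applied Clinical Research and "will not be revealed to the researchers until a study arm is completed".

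The only other sentence on routine release is in section 9.5: "Randomisation code is kept with the Unit of Applied Clinical Research until code can be broken". Section 9.1 mentions database lock but does not connect it with the code. Section 8.6 deals only with emergency unblinding of a single patient, by sealed envelope.

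The design section describes a "Double blind, prospective randomized parallel group placebo-controlled trial", and section 1.4 adds that "Patients are randomized in a 1:1 ratio to oxytocin or placebo". Follow-up consists of a day-30 visit and, under section 6.2.3, "A phone interview will be done at day 60".

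**The concern.** A parallel-group trial has no natural moment at which one arm ends and the other goes on. Both recruit together, and whichever happens to receive its last patient first finishes first. A list released at that moment covers everyone: once one arm's patients are named, the rest are known to be in the other. The trigger therefore allows the blind to be lifted while some patients are still under observation, which the opening sentence of the same section rules out.

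What is at stake is the outcome data collected after release and the decisions still open before lock. Relapse and alcohol intake over the four outpatient weeks are listed as primary for Phase 2 (section 2.1) and are self-reported at day 30. The day-60 contact is a telephone AUDIT interview. Data corrections, and the judgement of who showed full adherence and so belongs to the per-protocol population (section 10.3), could also still be open. With about 20 patients per arm, a few records carry some weight.

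**Working it through.** **The texts side by side.** Section 10.2.2 gives one duration for blinding (the study) and one earliest release time (one arm). Section 9.5 gives no event. Section 9.1 names a lock but attaches no release rule to it. So the arm-completion clause is the only concrete trigger, and it falls earlier than the end of the study.

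**How much earlier.** The protocol gives no figure on this point; its sample-size calculation is not affected. The size follows from these inputs:
- "40 patients will be included in this trial" (section 4.2), at 1:1 (section 1.4).
- "Anticipated recruitment period: 12 months" (section 3), taken as 365 days. Even accrual is an assumption.
- Day-30 visit and day-60 interview (sections 6.1 and 6.2.3).
- Allocation scheme: not stated. Simple, fixed 20:20, blocks of 4 and blocks of 8 are each tried as assumptions.

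Every patient has the same follow-up, so the first arm to complete is the one whose last patient entered earlier. The patients still outstanding are those at the end of the entry sequence who all belong to the other arm.

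*Number outstanding.* In a randomly ordered set of m patients per arm, the expected number of one arm's patients after the last of the other is m/(m+1). Counting both possibilities gives 2m/(m+1):
- fixed 20:20 (m = 20): 40/21 = 1.90
- blocks of 4 (m = 2 in the final block): 4/3 = 1.33
- blocks of 8 (m = 4): 8/5 = 1.60
- simple randomisation: very close to 2

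*Time gap.* With 40 evenly random entry times over 365 days, the mean spacing is 365/41 = 8.9 days. The gap between the two arms' last entries is then about 1.33 × 8.9 = 11.9 days to 2 × 8.9 = 17.8 days.

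Simulation of the four schemes agrees: 1.3 to 2.0 patients and 12 to 18 days.

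**Reading A: completed means through day 60.** At release:
- other-arm patients still awaiting day 60: 1.3 to 2.0 on average
- still awaiting day 30: below 0.4 on average under every scheme
- any patient still unenrolled: about 0.3% to 3% of simulated trials, because this needs a gap of more than 60 days

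The oxazepam total and the CIWA-Ar scores that drive it are fixed by day 3 (sections 7.1 and 7.2). They are therefore almost never exposed on this reading.

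**Reading B: completed means fully enrolled.** At release, the patients unenrolled or short of day 60 are:
- the 1.3 to 2.0 of the other arm still to enter, whose allocation would be known in advance
- the patient who has just completed the arm: 1
- those who entered in the previous 60 days: about 60/8.9 = 6.7

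The sum is about 9.0 to 9.7 of 40; simulation gives 8.9 to 9.6.

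*A special case of reading B.* If patients were allocated by coin flip until one of two fixed arms of 20 filled, the expected number left would be 40 × C(40,20)/2^40 = 5.0. The protocol describes no such scheme.

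**The case against.** The best defence is that this is a drafting slip. The first sentence of section 10.2.2 states the intent, database lock is a known milestone, and arm may have been written for study. The clause also sets an earliest time for release and does not order it. It speaks of researchers, while a separate sentence, with no end date, says that clinicians, staff and patients will not know which bottles are active. All of this is fair. It means that premature release is permitted, not planned, and that release to ward staff cannot be assumed. But it does not remove the contradiction, because no other passage supplies a different trigger.

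A reader might infer something stronger: that late allocations become predictable and that the remaining CIWA-Ar scoring, and so the oxazepam doses, would be done with knowledge of treatment. The documents do not support that as the ordinary case. With contacts at days 30 and 60, an arm is most naturally complete when its patients have finished them, and on that reading almost everyone has been enrolled and discharged. The inference needs the fully enrolled reading, and the figure of about five known allocations also needs the assumed coin-flip scheme.

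A reader might also count everyone in follow-up when the last patient enters: 40/12 = 3.3 per month, so about 3 awaiting day 30 and 6.7 awaiting day 60. That counts both arms at the end of recruitment, which is not the moment section 10.2.2 names.

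Two further points stand. The day-60 AUDIT interview, the contact most often exposed, is not a listed primary or secondary endpoint. And the procedure for agreeing analysis populations before the code is broken can properly sit in a statistical analysis plan, so its absence here is no fault.

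**Conclusion.** Wrong as written: an internal contradiction with a modest expected effect. The rule for releasing the code does not match the rule for keeping the blind, and section 9.5 does not settle it.

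On the natural reading the exposure is one or two patients' late follow-up, chiefly the day-60 interview, plus access to the code before database lock. On the less natural reading it reaches about a quarter of the trial and includes one or two foreseeable allocations. The sizes rest on even accrual over 12 months and on the allocation schemes tried; the contradiction rests on the text alone. Nothing here shows that the sponsor meant to unblind arm by arm, or that the oxazepam comparison is compromised.

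**What to change.** In section 10.2.2, replace the arm-completion clause with a statement that the code is released to researchers and analyst only after the last randomised patient in both arms has completed the day-60 contact or withdrawn, and the database has been locked. Name emergency unblinding of a single patient under section 8.6 as the only exception. Put the same wording in section 9.5 in place of the undefined release event.

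The cost is two sentences. No visit, sample size or analysis changes. The only practical consequence is that the researchers may wait a few weeks longer for the code than the present text allows.
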